## Abstract

**Background:**

Genomic sequencing in cancer (both tumour and germline), and development of therapies targeted to tumour genetic status, hold great promise for improvement of patient outcomes. However, the imminent introduction of genomics into clinical practice calls for better understanding of how patients value, experience, and cope with this novel technology and its often complex results. Here we describe a protocol for a novel mixed-methods, prospective study (PiGeOn) that aims to examine patients’ psychosocial, cognitive, affective and behavioural responses to tumour genomic profiling and to integrate a parallel critical ethical analysis of returning results.

**Methods:**

This is a cohort sub-study of a parent tumour genomic profiling programme enrolling patients with advanced cancer. One thousand patients will be recruited for the parent study in Sydney, Australia from 2016 to 2019. They will be asked to complete surveys at baseline, three, and five months. Primary outcomes are: knowledge, preferences, attitudes and values. A purposively sampled subset of patients will be asked to participate in three semi-structured interviews (at each time point) to provide deeper data interpretation. Relevant ethical themes will be critically analysed to iteratively develop or refine normative ethical concepts or frameworks currently used in the return of genetic information.

**Discussion:**

This will be the first Australian study to collect longitudinal data on cancer patients’ experience of tumour genomic profiling. Findings will be used to inform ongoing ethical debates on issues such as how to effectively obtain informed consent for genomic profiling return results, distinguish between research and clinical practice and manage patient expectations. The combination of quantitative and qualitative methods will provide comprehensive and critical data on how patients cope with ‘actionable’ and ‘non-actionable’ results. This information is needed to ensure that when tumour genomic profiling becomes part of routine clinical care, ethical considerations are embedded, and patients are adequately prepared and supported during and after receiving results.

**Trial registration:**

Not required for this sub-study, parent trial registration ACTRN12616000908437.

## Background

Despite treatment advances in recent years, survival rates in some cancers have only minimally improved. [1] As such, there is a significant need for new approaches to increase patient survival and reduce morbidity. Tumour genomic profiling (TGP) and personalized treatment offer new opportunities for improvement in cancer outcomes. It is anticipated that TGP will increasingly allow identification of cancer patients who will benefit from targeted drugs and immunotherapy approaches, in contrast to current ‘scatter-gun’ approaches of chemotherapy and radiotherapy. [2]

There are generally two types of genomic sequencing in the cancer context: TGP and germline genomic sequencing (GGS). TGP involves laboratory analysis of somatic tissue to identify somatic driver mutations in tumours, whereas GGS involves examination of the entire genome through a blood sample seeking germline variants associated with cancer predisposition syndromes. This study focuses on TGP. A second study examining the psychosocial, behavioural and ethical issues and outcomes of GGS on cancer probands and their blood relatives is also underway and its protocol will be published separately. The two sub-studies together represent The P (psychosocial) i(n) Ge (genomics) On (oncology) PiGeOn project.

TGP involves panel or whole genome testing of DNA derived from tumours. This may identify gene variants that can inform choice of treatments targeting the specific gene variants present in the tumour. TGP can identify somatic variants that: i) affect treatment (clinically actionable); ii) do not affect treatment (non-actionable); or iii) are of uncertain significance. TGP can be followed by further confirmatory testing if it is suspected that gene variants may have a germline origin (and therefore may also be relevant to the patient’s family).

The promise of genomic medicine will only be realised if patients understand and benefit from identification of gene variants; that is, they need to understand the chances of finding actionable variants, and any potential implications of results. While uncertainty in terms of potential information available pervades TGP less than GGS due to the smaller scope of testing, there remains an element of uncertainty due to the poor prognosis of most patients and the uncertainty of the results being clinically actionable, and also the chance of finding a germline variant with the subsequent implications of testing for the recipient’s blood relatives. Practitioners who obtain consent for TGP face the challenges of conveying these uncertainties to both ensure informed choice regarding testing and to mitigate any unrealistic expectations.

Further, although uncertainty may be shared among stakeholders, such as during education sessions between physician and patient, the extent of intricacy within genomic testing can lead to both parties remaining unaware of their areas of ignorance. [3] The expected future expansion of TGP to other healthcare providers and non-genetics specialists raises questions of 1) how best to approach the consent process, and 2) about disclosure of complex results when providers may have limited training and/or expertise in genetics. While patient autonomy, informed consent and shared decision-making are established standards in health care, there are no guidelines on how patients should be engaged with regard to the decision to have TGP, nor how uncertainty should be approached in this complex area. Debate is ongoing. [4]

We have little understanding of the ethical, psychosocial and behavioural implications of providing cancer patients with results from TGP, and whether it will be experienced differently to other medical tests. The published evidence has been gathered primarily from research participants who may or may not have cancer, where the potential benefits of a gene variant being present (such as access to novel therapeutic options) differ. Several North American studies [5–7] presenting hypothetical scenarios to cancer patients regarding TGP, found the majority would be interested in tumour profiling, although the participants felt they had insufficient knowledge to make an informed choice. While a majority of patients in hypothetical scenarios expressed a willingness to undergo TGP for personalized treatment, many also expressed significant concerns about potential psychological harm, cost and discrimination. Misunderstandings about TPG were also noted. [5]

Overall, very little is known about the knowledge, preferences, attitudes and values of cancer patients who have actually undergone TGP, their experience of uncertainty, their behaviour on receipt of TGP results, or the psychological effects these results may have. Only a handful of studies have explored responses in cancer patients who have actually been offered TGP. These have primarily noted patient report of information overload and misunderstanding, leading to unrealistic expectations, anxiety and uncertainty [8–10]. Patient hopes of benefit from TPG were enhanced by the promise of novel and targeted treatment but challenged by non-findings or by limited access to relevant trials. [8] To our knowledge, none of the studies of patients who have actually undergone TGP testing have reported longitudinal data.

Oncologists were among the first clinicians to incorporate TGP into routine management to guide treatment choice. Unifocal profiling goes back to estrogen receptor status testing in breast cancer and then EGFR mutation in lung cancer, with recent testing of the KRAS gene in colorectal cancer and the BRAF gene in melanoma. [11, 12] It is critical to explore how patients value and experience TGP, and cope with uncertainty, non-actionable results and incidental findings, as well as informative findings, as TGP increasingly enters routine oncological clinical practice.

This paper outlines the protocol of the first Australian study collecting longitudinal data on cancer patients’ experiences of TGP over time.

### Guiding theory

The design and measures for the study are guided by Protection Motivation Theory [13] and Differentiation and Consolidation Theory. [14] Protection Motivation Theory proposes that we protect ourselves based on the perceived severity and probability (vulnerability) of a threat, perceived efficacy of preventive behaviour, and perceived self-efficacy in performing the preventive behaviour. Differentiation and Consolidation theory states that decision-making reflects a process of gradual differentiation including: identifying options with perceived important attributes, prioritising one or two options based on highly ranked attributes and reconsidering an initial preference based on further information. This is followed by a consolidating process, which focuses on one’s values, and future possible outcomes, to favourably reinforce the chosen option and thereby prepare for potential threats, regret and doubt.

In this setting, protection motivation will be the result of perceived susceptibility to disease progression and death, and fear of cancer progression, as well as participant knowledge of, attitudes to, and value given to, TGP (as a strategy to guide more effective treatment and thus reduce the threat of disease progression). Patients who perceive TGP to be valuable will be more likely to remain satisfied with their decision to undertake TGP, regardless of results, and to act on positive results by joining appropriate clinical trials of tailored treatments. Intolerance of uncertainty may make TGP less attractive and increase the likelihood of regret, doubt and poor psychological outcomes.

## Methods/design

### Aims and hypotheses

The aim of this study in adults with advanced cancer undergoing TGP is to:*Before and after receipt of results:* evaluate knowledge of TGP, preferences for genetic information, attitudes (positive and negative) and the value placed on TGP;*After receipt of results:* identify behavioural, decisional and psychological outcomes from TGP along with their respective predictors; andContextualize the findings via a critical bioethics analysis.

Specific hypotheses are that:At baseline (after giving informed consent to undergo TGP), advanced cancer patients will have moderate to poor knowledge about TGP (< 55% correct on knowledge scale).At baseline, advanced cancer patients will have primarily positive attitudes to, and highly value, TGP.Of advanced cancer patients *who receive an actionable result*, most will:Pursue personalised treatment in a clinical trial setting (behavioural outcomes).Cope well with results, and experience low decisional conflict and regret and high decisional satisfaction (decisional outcomes).Have higher hope, less cancer-related anxiety, lower fear of cancer progression and lower general anxiety and depression than those who do not receive actionable results (psychosocial outcomes).Those advanced cancer patients who have *no actionable variants identified* will:Struggle to cope with non-results (decisional outcomes).Have levels of hope, cancer-related anxiety, fear of cancer progression and general anxiety and depression similar to published results for advanced cancer patients who have not undergone TGP, within 1 month of receiving results and 5 months later (psychosocial outcomes).5.Predictors of behavioural, decisional and psychological outcomes within 1 month of receiving results and 5 months later, will include:Age, education level, ethnicity, and gender;Tolerance of uncertainty and baseline knowledge; andPreferences and attitudes to TGP.

Methodology in critical bioethics analysis is not hypothesis-driven and to this end there are no hypotheses relating to this part of the analysis.

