### Procedure for PiGeOn

Patients will provide consent to MoST staff for the psychosocial (PiGeOn) sub-study at the same time as they give consent to the parent TPG program. Thus at baseline they will have already considered and given consent to TGP, but not yet had TGP. Participants will be asked to complete a questionnaire (hard copy, online or via telephone if they prefer) at baseline (T0), 1 to 4 weeks after receiving TGP results (T1, approximately 2–3 months post baseline), and at 2 months (T2) after T1. These timeframes have been chosen to allow impacts of the test results to be captured in both the short-term (when a treatment decision is being made) and longer-term (while undergoing or near to completion of targeted therapy, if adopted). A small subset (around 20–40 participants) will be invited to participate in semi-structured interviews at the same assessment time points to explore in more detail attitudes towards TPG and its associated psycho-social, behavioural and ethical aspects. See Fig. 1.

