### Fear of cancer progression

Three items from the Concerns about Recurrence Questionnaire [30], adapted to measure fear of cancer progression. High scores indicate greater fear.

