### Sample size

The MoST study plans to recruit 1000 patients over three years. Thus, with a conservative retention and survival estimate of 75%, this is reduced to at fewest 469 patients. With this sample size estimate, assuming 15% of patients receive an actionable result and using a significance level of 0.05, this project: has 90% power to detect a mean change of 5.8 and 2.6 points on the Impact of Events scale for patients with actionable and non-actionable results respectively (paired t-test, SD = 15) [32] and a mean difference of 4.5 points between patients with actionable and non-actionable results; Multiple regression with at most 24 explanatory variables (including dummy variables) has 90% power to detect significant categorical variables with 5 categories (largest possible categorical variable) when that predictor explains greater than 3.6% of the residual variance, or to detect a continuous variable when it explains more than 2.3% of the residual variance. For patients with actionable results only (at fewest 70), at 80% power the minimum variance explained for continuous variables would be 12% of the residual variance, and 15% for binary predictors. For logistic regression when outcomes are on average equally likely the power to detect an odds ratio of 1.4 is 95% or 80% when the other covariates explain zero, or 37% of the outcome variance respectively. For only those with actionable results, there is 80% power to detect an odds ratio of 2.14 or greater if the other outcomes explain zero outcome variance.

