### Quantitative data analysis

Mean differences in outcomes will be compared using t-test (continuous) or chi-squared tests (dichotomous). Non-parametric tests will also be used where appropriate. Temporal changes in scales will be investigated by calculating the difference between time-points. Multiple (continuous outcomes) or logistic (dichotomous outcomes) regression will be used to adjust for the effect of confounders and identify predictors of outcome. Linear mixed models and logistic mixed models will be carried out in R: A language and environment for statistical computing using package nlme for the linear mixed model and lme4 for the logistic mixed model. Assumptions of normality of residuals and homogeneity of variance will be checked visually though diagnostic residual plots. Multivariable models will be constructed with the inclusion of all potential confounders, and those predictors that show weak evidence for an association with the outcome in univariate analysis. Backwards elimination followed by forwards addition will be used to select predicting variables in the final model. Known and identified confounders will be included regardless of their statistical significance. Collinear independent variables will be identified and removed.

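### Hypothesis 4 predicts similarity to published values while the stated tests and power address only differences or associations, and the second time point in hypotheses 4 and 5 conflicts with T2

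*Protocol article*

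**What the plan says.** **Hypothesis.** In the Aims and hypotheses section, hypothesis 4 concerns patients with no actionable variant. Their hope, cancer-related anxiety, fear of progression, and general anxiety and depression are predicted to be "similar to published results for advanced cancer patients who have not undergone TGP, within 1 month of receiving results and 5 months later". Hypothesis 5 uses the same pair of time points for predictors of outcome.

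**Methods.** The Quantitative data analysis section states: "Mean differences in outcomes will be compared using t-test (continuous) or chi-squared tests (dichotomous"). It adds non-parametric tests, change scores and mixed models, and says: "Multiple (continuous outcomes) or logistic (dichotomous outcomes) regression will be used to adjust for the effect of confounders and identify predictors of outcome". It describes no comparison with published values and no criterion for calling two means similar. Every figure in the Sample size section is power to detect a difference, a change or an association.

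**Timing.** The Procedure for PiGeOn section places T1 at 1 to 4 weeks after results, "and at 2 months (T2) after T1". Table 1 agrees and lists no later survey. The Abstract gives surveys at baseline, three and five months.

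**The concern.** A test of difference cannot establish similarity. Failing to reject equality may mean that the means are close, or that the comparison is imprecise. Rejecting it may mean a real departure, or a trivial gap measured precisely. The result depends on both the gap and the precision, whereas the hypothesis concerns the gap alone.

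The benchmark comparison carries weight here. Hope, general anxiety and depression, and the Impact of Events Scale are not collected at baseline (Table 1 and the note under Coping with uncertainty). On those scales the published values are the only stated reference for patients who have not had tumour genomic profiling.

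The timing wording is a second, separate matter. If the hypotheses are followed literally, scores taken two to three months after results could be reported as five-month outcomes.

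**Working it through.** **Inputs from the Sample size section.** N: "this is reduced to at fewest 469 patients". Actionable share and alpha: "assuming 15% of patients receive an actionable result and using a significance level of 0.05". This gives 469 × 0.15 ≈ 70 actionable and 469 − 70 = 399 non-actionable patients. SD = 15 is given there for a paired t-test; using it as the SD of score levels is an assumption. Tests are taken as two-sided, since sidedness is not stated.

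**The plan's own figures.** The article claims that the study "has 90% power to detect a mean change of 5.8 and 2.6 points on the Impact of Events scale", for actionable and non-actionable patients respectively. With (1.960 + 1.282) × SD/√n:

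- n = 70: 3.242 × 15/√70 = 5.81, which matches 5.8.
- n = 399: 3.242 × 15/√399 = 2.43, not 2.6. Power at 2.6 is about 93%, and 2.6 fits n of about 350.

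That mismatch is a separate matter. Both figures are power to detect change; neither concerns similarity to a benchmark.

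**Precision of the benchmark comparison.** If the published mean is treated as fixed, SE = 15/√399 = 0.751 and the 95% half-width is 1.96 × 0.751 = 1.47 points, or 0.1 SD. If the published sample has size m and SD 15 (m is assumed), SE = 15 × √(1/399 + 1/m). The chance that the difference test is non-significant at a true gap d is 1 − [Φ(d/SE − 1.96) + Φ(−d/SE − 1.96)]. Taking d = 2.6, the change the plan itself chose as detectable in this group:

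| Published sample | 95% half-width (points) | Non-significant at a true gap of 2.6 |
|---|---|---|
| treated as fixed | 1.5 | 7% |
| 400 | 2.1 | 31% |
| 200 | 2.5 | 48% |
| 100 | 3.3 | 66% |
| 50 | 4.4 | 79% |

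The same true gap would be found or missed largely according to the size of the published study. In the other direction, against a fixed benchmark a true gap of 1 point is significant in about 27% of cases (1 − 0.73), and a gap of 2 points in about 76% (1 − 0.24).

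**Sensitivity.** Half-widths scale with the SD. At SD 10 or 20 (assumed) the fixed-benchmark value is 1.96 × 10/√399 = 0.98 or 1.96 × 20/√399 = 1.96. With the 5–10% actionable rate in the Discussion, the non-actionable group is 446 to 422 and the half-width is 1.39 to 1.43.

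**Is an equivalence criterion feasible?** With two one-sided 5% tests and a true difference of zero, power = 2Φ(margin/SE − 1.645) − 1.

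- Fixed benchmark, assumed margin 3 points (0.2 SD): 2Φ(3/0.751 − 1.645) − 1 = 0.98.
- Published sample 200, assumed margin 4.5 points (0.3 SD): SE = 1.30, so 2Φ(4.5/1.30 − 1.645) − 1 = 0.93.
- Smallest margin with 90% power, 2 × 1.645 × SE: 2.5 points (fixed benchmark) or 4.3 points (m = 200).

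**Time points.** The Parent study section puts results at about 11 weeks. At 4.345 weeks per month:

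- T1 = 12 to 15 weeks = 2.8 to 3.5 months after baseline.
- T2 = T1 + 2 months = 4.8 to 5.5 months after baseline, which fits the Abstract.
- Results to T2 = 1/4.345 + 2 to 4/4.345 + 2 = 2.2 to 2.9 months.
- T1 + 5 months = 7.8 to 8.5 months after baseline, when no survey is scheduled.

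**The case against.** The strongest reply is that the article condenses a fuller protocol and analysis plan. The Quantitative data analysis section is generic and assigns no test to any hypothesis. A named benchmark, a margin and a confidence-interval rule may sit in a document not shown, and their absence alone is no fault. That stands. What remains is that the article fixes a similarity hypothesis and also states its methods and power, and the two do not fit.

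A reader might infer that the investigators will treat a non-significant test as proof of similarity. No such rule is written, so the supportable statement is that it could happen. Nor is a shortage of patients the documented risk: 469 is given as a floor after attrition. At 399 patients and a fixed benchmark the estimate is precise, and the risk comes mainly from the unstated criterion and from sampling error in the published mean.

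A reader might also infer that fear of progression has no published comparator. The article says only "Three items from the Concerns about Recurrence Questionnaire [30], adapted to measure fear of cancer progression". Whether comparable scores exist depends on sources outside the documents, so it is a point to check.

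On timing, a reader might infer that the study measures nothing at five months, or that the published comparison would be made at the wrong time. Neither is supported. T2 falls about five months after baseline, so the likeliest explanation is a wrong anchor. Nothing says the benchmark is matched on time, and its patients have no results date to match.

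Finally, the Abstract's primary outcomes are knowledge, preferences, attitudes and values, so this is not a primary comparison. That limits the weight of the point but does not remove it.

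**Conclusion.** The point holds in two limited parts and should be corrected.

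First, the methods and power that the article states cannot by themselves support hypothesis 4. On the Impact of Events Scale, a gap of about 1.5 points would be significant against a fixed benchmark, and about 2.5 points against a published sample of 200. A true gap of 2.6 points would go undetected in 7% or 48% of cases respectively. These figures rest on 399 non-actionable patients, SD 15 for levels, an assumed published sample size and two-sided 5% tests. The mismatch between hypothesis and method does not depend on them.

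Second, the second time point in hypotheses 4 and 5 contradicts the assessment schedule. As anchored there, it falls where no survey is planned. The available assessment, T2, is 2.2 to 2.9 months after results. This is a mislabelled time point in the hypotheses, not a missing assessment.

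**What to change.** - For each scale in hypothesis 4, name the published benchmark and pre-state a justified margin. Declare similarity only if the 90% CI for cohort mean minus published mean, with the published standard error included, lies wholly within the margin.
- Otherwise, or where no comparable published score or defensible margin exists, report the difference and its CI without claiming similarity. Check this in particular for the three adapted fear-of-progression items.
- In hypotheses 4 and 5, replace the five-month wording with T2 (2 months after T1, about 5 months after baseline), so that outcomes are not reported as five months after results.

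The cost is some rewording and one interval per scale. The real burden is justifying the margins: the documents offer no basis for any, and the 3- and 4.5-point values above only show feasibility. No extra patients or surveys are needed to apply the criterion, although a small published sample may leave the interval too wide to support a similarity claim.
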